		**Study period**					
	**Enrolment**	**Baseline assessment**	**Allocation**	**Intervention**	**Outcome assessment**		
**Timepoint**		***t***_**1**_			***t***_**2**_	***t***_**3**_	***t***_**4**_
**Enrolment:**	X						
**Eligibility screen**							
**Informed consent**	X						
**Allocation**			X				
**Interventions:**				X			
***A: Self-management program (SEMPO)***							
***B: Treatment as usual***				X			
**Assessments:**		X			X	X	X
***Primary outcome assessment***** (***self-efficacy)*							
***Secondary self-selected outcome assessment**** (symptom burden, physical, cognitive, emotional functioning, return to work)*		X			X	X	X
***Other**** (Resilience, quality of life, intervention changes and satisfaction, disability and functioning, health communication, and utilization of services*							
***Determination of costs during the study period***		X				X	X

*t1 *time point one, baseline assessment at approximately 3–4 months post injury; *t2 *time point two, follow-up at end of intervention at approximately 8–10 weeks after the baseline assessment; *t3 *time point three, follow-up at 3 months after intervention;* t4 *time point four, follow-up at 6 months after intervention

### Outcomes

#### Patient characteristics

The following sociodemographic variables will be registered at baseline: age, sex, marital status, educational level, living conditions, employment status, and annual income. Changes in living conditions, employment status and annual income will be recorded at the follow-ups.

#### Injury-related characteristics

Clinical and injury-related variables included comorbidities, diverse injury characteristics, and the trauma severity scores: the Abbreviated Injury Scale (AIS), Injury Severity Score (ISS), and NISS [22], length of hospitalization and medical treatment modalities, discharge place, and symptom burden along with screening of cognitive function in patients with suspected impaired cognitive function (MMS < 20). The trauma severity scores will be validated by data registered by certified AIS registrars in the hospitals’ trauma registries.

#### Outcome measures

When evaluating the effectiveness of complex interventions, it is recommended to use more than one outcome measure [25]. As the intervention aims to improve patients’ level of self-efficacy, the Trauma Coping Self-efficacy Scale [26] was chosen as the primary outcome with the 6-month follow-up (T4) being the endpoint. Secondary outcomes comprise domains such as symptom burden, physical and cognitive functioning, emotional distress, and return to work. Patients will nominate their target problem areas in their own words [27]. They will also be asked to nominate one self-selected outcome measure based on a presented list of domain-related measurements related to fatigue, sleep, pain, physical functioning, cognition, emotional functioning, and vocation. The rationale for including a patient-preferred outcome measure to ensure participant involvement and patient-centered outcome measurement. Their preferred outcome domain will be established as their self-selected secondary outcome at baseline. Additional outcomes include health-related quality of life, resilience, disability and global functioning, and patient impression of changes. All outcome measures are validated and presented in Table 2. The Trauma Coping Self-Efficacy Scale, the communication with physicians, and the Health Literacy Questionnaire were translated into Norwegian using the established translation procedures by a professional translation service (Forward translation; Expert panel discussion; Back-translation; Final version) [28]. Data for cost-effectiveness and cost-utility will be based on patient-reporting surveys of the type and frequency of received health care services. See Table 2 for an overview of the included outcome measures.

**Table 2 Tab2:** Description of outcome measures utilized in the RCT

Domain:	Outcome measures:	Description:	Time point
**Primary outcome measures for all patients**			
Self-Efficacy	Trauma Coping Self-Efficacy (ref) [26]	Confidence in managing health problems and emotional functioning	T1–T4
**Secondary individual self-selected outcome measures by domain**			
Symptom burden	Rivermead Post-Concussion Symptom Questionnaire [29] Fatigue Severity Scale [30] Insomnia Severity Index [31] Brief Pain Inventory [32]	Symptom burden Fatigue Sleep disturbance Pain	T1–T4
Physical function	Short Physical Performance Battery [33] International Physical Activity Questionnaire Short Form [34]	Physical functioning level Overall physical activity and specific levels of intensity	T1–T4
Cognitive function	Cognitive Failures Questionnaire (CFQ) [35] Cognitive items Rivermead (memory, concentration, and mental speed) [29]	Self-reported cognitive failures Self-reported cognitive deficits	T1–T4
Emotional distress	Patient Health Questionnaire-9 [36] Generalised Anxiety Disorder-7 [37] Impact of Event Scale – Revised [38]	Depression Anxiety Post-traumatic stress	T1–T4
Return to work	Full-time/part-time (percentage); hours per week	Vocational participation	T1–T4
**Other outcome measurements for all patients**			
Resilience	Resilience Scale for Adults [39]	Level of Resilience	T1–T4
Health status (HRQL)	EuroQol five-dimensional questionnaire (EQ-5D) [40]	Health-related quality of life	T1–T4
Individual injury-related problem areas	Target Outcomes [27]	Individual target problem areas and their severity	T1–T4
Evaluation of changes and intervention satisfaction	Patient Global Impression of Change [41] Intervention satisfaction (intervention group only)	Level of satisfaction with intervention/ change	T2–T4 T2
Disability	WHO Disability Assessment Scale (WHODAS) [42]	Health and disability	T1–T4
General functioning	Glasgow Outcome Scale – Extended (GOSE) [43]	Global outcome	T1–T4
Communication	Communication with physicians [15] Health Literacy Questionnaire [44]	Communication with health care providers Capacity to obtain and understand health information	T1–T4
Health care utilization	Type and frequency of health care services received using a patient-reported survey. Health care services comprise secondary care services, primary care, specialist care, rehabilitation, and home- and community-based care, assistive devices, and informal care	Number of visits and type of health care services	T1–T4

### Process evaluation

Conducting a process evaluation as part of a randomized trial is recommended by the British Medical Research Council as it can add valuable knowledge about causal mechanisms, fidelity, and contextual factors that may influence both implementation of the intervention and variations in outcomes [25, 45]. In this study, the process evaluation will be based on information from the interventionists and participants using a mixed method approach by combining quantitative and qualitative data. This includes registration of participation rate, number of consultations apart from sessions and follow-ups, and direct and indirect time use of each consultation. Further, the completion of intervention due to protocol, variations, and reasons for non-compliance will be recorded. After the completion of the SEMPO, patients will be asked to evaluate the content and their satisfaction with the intervention using a semi-structured interview form.

### Interventions

#### Intervention group: self-management program (SEMPO)

The SEMPO program was developed by experienced clinicians and researchers and is based on well-known principles from the self-management concept and established rehabilitation strategies [11, 46]. Thus, SEMPO adheres to theories of self-efficacy as a mean of coping [11, 47]. The program aims to enhance self-efficacy by strengthening patients’ skills and confidence in managing the persisting consequences of the injury, as well as enhancing their health literacy and problem-solving competence. The program integrates components from evidence-based rehabilitation strategies within relevant functional domains [48, 49] to fit the symptom burden of the trauma population. User involvement was an essential part of the development of the intervention, and we collaborated with a user panel consisting of persons living with persistent injury-related consequences and representatives from the involved user organization, the National Association of the Traumatically Injured (LTN). In addition, the program has been adjusted after feedback from a test trial of the intervention (*n* = 5 persons), where patients were interviewed at the end of the testing regarding perceived usefulness and feedback on program content.

The SEMPO is delivered through 8 weekly 2.5-h sessions to groups consisting of 4–7 patients. A group format is chosen because social encouragement is considered a powerful means of increasing self-efficacy, thus SMS intervention delivered in groups is regarded as effective for behavior change, skills enhancement, and modeling [11]. Different components, such as psychoeducation, guided skills mastery, learning and practicing helpful compensatory strategies, and problem-solving techniques are integrated. In the weekly group sessions, topics with tailored psycho-educative content are presented and action plans reviewed, modified, and discussed in the group to help with problem-solving and address challenges. The manual will provide a fixed framework for the intervention, but action plans will be individualized and based on self-reported problems and individual challenges. In each session, patients will establish their own action plans containing achievable short-term weekly goals and related strategies. The program also includes a workbook, containing material from each session, self-monitoring schemes of weekly goal setting and goal attainment, as well as practice tasks between sessions (e.g., problem-solving of personal difficult tasks, strategy training of emotional worries). According to Bandura’s theory of self-efficacy [47], these ingredients may enhance a person’s self-confidence in managing trauma-related symptoms, problems in daily life activities, and participation. A tele-health version of the SEMPO intervention will be available for patients who prefer this or have to travel long distance to the hospital. In the tele-rehabilitation version, all participants will attend digitally, and the intervention will be delivered with the same content, frequency, and in-group mode. An overview of the intervention topics is displayed in Table 3.

**Table 3 Tab3:** Overview of the intervention topics

No	Intervention topics
1	Introduction intervention/common injury consequences/action plans
2	Pain, use of medication, and nutrition
3	Active living, physical function, and exercise
4	Cognitive symptoms and compensatory techniques
5	Fatigue and sleep management
6	Managing psychological distress
7	Use of community resources and communication with health professionals
8	Summary and generalization of action plan for future problem areas

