### Sample size

The sample size was estimated based on the primary outcome, the Trauma Coping Self-Efficacy Scale questionnaire [26]. The questionnaire is a 9-item scale answered on a scale ranging from 0 (not capable) to 7 (totally capable). A mean difference in the Trauma Coping Self-Efficacy Scale of 0.6 between baseline and follow-up between the groups is considered as a clinical relevant difference (ref). In order to detect a mean between-group difference of 0.6 with an estimated standard deviation of 1, equal allocation to both groups, 80% power, and a significance level of 5%, we will need to include a minimum of 45 patients in each group and a total of 90 participants [51]. With an assumed attrition rate of 20%, 110 patients will be included (i.e., 55 patients in each group). The sample size calculation was done based on the classical randomization arm (RA), and we aim to achieve the same power in the self-selection (SA) arm. However, the SA is considered an exploratory part of this study to evaluate the influence of patients’ treatment preferences. According to a previous longitudinal study at OUH, approximately 310 patients with trauma-related disability from 18 to 72 years of age may meet the inclusion criteria [52]. Based on previous studies, approximately 70–80% will be eligible for inclusion, resulting in 218–249 eligible patients per year.

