### Statistical methods

Sociodemographic, clinical, and injury-related characteristics and outcome data will be presented using descriptive statistics. Independent sample *t*-test will be used for between-group mean comparisons for normally distributed continuous data, and Mann–Whitney *U*-tests for skewed data. For comparison of categorical data, chi-square tests or Fisher’s exact test will be used. To investigate the effectiveness of the intervention on self-efficacy, symptom burden and disability, and patient impression of change, mixed-effect models will be used to account for repeated measurements by patients. Time and time-by-treatment interaction will be used as fixed effects in these models. The linear mixed effects model will give estimated mean values for all time points (T1, T2, T3, and T4), changes from baseline, and between-group differences from baseline with 95% confidence intervals. The models will first be performed separately within the classical RCT and self-selected groups, and if reasonable, merged together. Possible confounders or mediators will be included when analyzing the self-selected group. To reduce the risk of dropout bias, the analyses will be based on an “intention to treat” principle by analyzing all patients in the group they were randomized to, regardless of whether they participated in or completed the intervention. A significance level of 5% will be used.

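### SEMPO is given in groups of 4–7, but the stated model and the 80% power make no allowance for correlation within a group, which would matter if that correlation is more than trivial

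*Protocol article*

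**What the plan says.** In the protocol article, the section on the intervention group states: "The SEMPO is delivered through 8 weekly 2.5-h sessions to groups consisting of 4–7 patients". It gives the reason for the format: encouragement from other group members is expected to raise self-efficacy. Action plans are reviewed and discussed in the group, and telehealth groups meet wholly online. The control-group section describes usual municipal or other rehabilitation care, with no groups formed by the trial. Trial-made clustering can therefore arise in one arm only.

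Under Statistical methods, "mixed-effect models will be used to account for repeated measurements by patients", with time and time-by-treatment as fixed effects. No therapy-group term is named. The models are run separately in the randomization arm (RA) and the self-selection arm (SA), and merged if that seems reasonable.

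The Sample size section takes a target difference of 0.6 and an SD of 1, and states: "equal allocation to both groups, 80% power, and a significance level of 5%, we will need to include a minimum of 45 patients in each". It then allows 20% attrition and arrives at 55 per group, 110 in total, for the RA. It mentions neither an ICC nor a design effect.

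**The concern.** Patients who attend the same eight sessions share therapists, delivery mode and each other's influence. If that makes their later self-efficacy scores more alike than those of patients in different groups, they carry less information than the same number of independent patients. A model with only a patient-level random effect does not see this. Its confidence interval for the T4 contrast would be too narrow, and the test would reject a true null hypothesis more often than the nominal 5%. The 80% power, stated without qualification, would also contain no allowance for the loss. The error would favour SEMPO on the primary endpoint.

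**Working it through.** **Inputs from the protocol.** Difference 0.6, SD 1, equal allocation, 80% power, 5% significance (two-sided taken, because it reproduces the stated figure), 45 per group, 20% attrition, 110 enrolled, group size 4–7.

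**Assumptions, not in the protocol.** ICC 0.01 to 0.10; average group size m = 5.5 (midpoint of 4–7); total variance held at 1; one time point without baseline adjustment; completers per arm n = 110 × 0.8 / 2 = 44.

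**Step 1, the plan's own figure.** Normal approximation: 2 × (1.96 + 0.8416)² / 0.6² = 43.6, so 44 per group. The two-sample t-test gives 45 (power 80.4%), which is the stated number. It reproduces under independence, so no clustering allowance is hidden in it. At n = 44 and ICC 0, power is 80.4% by the normal approximation and 79.5% by the t-test.

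**Step 2, clustering in the SEMPO arm only.**
- Design effect in that arm: DE = 1 + (m − 1) × ICC
- True standard error: √[(DE + 1)/n]
- Ratio of true to naive standard error: R = √[(1 + DE)/2]
- Power: Φ(0.6/SE − 1.96)
- Type I error of the naive test: 2 × [1 − Φ(1.96/R)]

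Example, m = 5.5 and ICC 0.05: DE = 1 + 4.5 × 0.05 = 1.225; SE = √(2.225/44) = 0.225; R = √(2.225/2) = 1.055; power = Φ(2.668 − 1.96) = Φ(0.708) = 76.1%; type I error = 2 × [1 − Φ(1.858)] = 6.3%.

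| RA patients per group | ICC | DE | Power | Naive type I error |
|---|---|---|---|---|
| 5.5 (RA-only groups) | 0.01 | 1.045 | 79.5% | 5.3% |
| 5.5 | 0.05 | 1.225 | 76.1% | 6.3% |
| 5.5 | 0.10 | 1.450 | 72.0% | 7.7% |
| 2.3 (RA and SA mixed) | 0.05 | 1.065 | 79.1% | 5.4% |
| 2.3 | 0.10 | 1.130 | 77.8% | 5.8% |

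The 2.3 is an assumption. It corresponds to about 76 of the 110 SA patients choosing SEMPO: 5.5 × 55/(55 + 76) = 2.3.

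**Step 3, few groups.** The normal approximation ignores that 44 patients in groups of 5.5 make only 8 groups. With Satterthwaite degrees of freedom, power at m = 5.5 is 76.0%, 72.0% and 67.4% for ICC 0.01, 0.05 and 0.10.

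**Step 4, simulation.** With 45 per arm, 40,000 replicates and group sizes 4 to 7, a naive t-test rejected a true null in 4.9–5.3% of runs at ICC 0.01, 5.8–6.9% at 0.05 and 6.5–8.4% at 0.10.

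**Step 5, effect of baseline.** Time and time-by-treatment as the only fixed effects, read literally, hold the baseline means equal and give roughly the precision of a baseline-adjusted analysis. Take SD 1 as the raw-score SD and an assumed baseline–T4 correlation ρ. The residual variance is then a = 1 − ρ², and SE = √{[a + (m − 1) × ICC + a]/44}. For m = 5.5 and ρ = 0.3, 0.4 and 0.5, power is 79.5%, 82% and 86% at ICC 0.05, and 75%, 78% and 81% at ICC 0.10. At m = 2.3 it is at least 81% in all these cases. Type I error does not improve: 6.4–8.6% at m = 5.5 and 5.4–6.0% at m = 2.3.

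**The case against.** A reader might infer three stronger things, none of which the protocol supports.

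**That outcomes within a group are certainly correlated.** Social encouragement is meant to work in every group. It could raise the mean everywhere without making groups differ, and an ICC needs differences between groups. The manual gives a fixed framework, action plans are individual, and the endpoint falls six months after the last session. The rationale makes a positive ICC plausible but does not give its size, and at 0.01 the effect by design effect alone is negligible.

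**That real power is below 80%.** Step 5 shows that the planned use of T1–T4 data may offset the loss. Mixed groups would also weaken it in the RA. About 55 RA patients are to receive SEMPO over roughly 36 months of recruitment, or about 1.5 per month if accrual is even. RA-only groups of 4–7, started 3–4 months after injury, would be hard to fill. The protocol does not say whether RA and SA patients share groups, so this remains a likely reading and not a fact. Non-attenders kept in their randomized group would dilute clustering further.

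**That the protocol rules out a group effect.** It says what the mixed model is for, but does not list random effects or degrees of freedom. An analysis plan that is not shown could add a group term without contradicting it.

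These arguments lower the severity and the certainty about size. They do not remove the point. No analysis plan can put a clustering allowance into a sample size already stated without one, baseline adjustment leaves the type I inflation in place, and a merged RA and SA analysis would face the larger group size.

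**Conclusion.** The point holds in conditional form. The protocol fixes group delivery in one arm and gives a reason to expect group influence on the primary outcome. It describes a model and a sample size that recognise patient-level dependence only. For any positive ICC the naive standard error of the T4 contrast is too small: by 1% at ICC 0.01, 5% at 0.05 and 11% at 0.10, for RA-only groups of 5.5. Type I error is then about 5.3–7.7%, or 5.4–5.8% at ICC 0.05–0.10 if groups are mixed. Whether power falls short of 80% depends on the ICC, the group composition and the baseline correlation, none of which the protocol gives. This should be fixed. Confidence is high in the direction given a positive ICC, and moderate in the size.

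**What to change.** 1. Record a SEMPO group identifier as groups form, with one numbering across RA and SA, and state whether the two arms share groups.
2. Add to the primary model a SEMPO-group random effect that is active only for SEMPO participants and only at T2–T4, because T1 precedes randomization and group formation. Controls stand as singletons (a partially nested model). Use Kenward–Roger or Satterthwaite degrees of freedom. Apply the same structure to any merged analysis.
3. In the Sample size section, replace the unqualified 80% with power over an assumed ICC range, and state what baseline correlation, if any, is relied on.

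The cost is one variable, one model term and a paragraph of text. The interval becomes wider, the group variance is estimated from few groups and so imprecisely, and the stated power may look less favourable. The change itself needs no extra patients. Holding 80% by an unadjusted calculation would: at m = 5.5 and ICC 0.05 the evaluable number is 44.58 × (1 + 1.225)/2 = 49.6, so 50 per arm, or 100/0.8 = 125 enrolled against 110, before any loss from having few groups. Stating power honestly over a range is the proportionate course.

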#### Criteria for discontinuing or modifying allocated interventions

The intervention will be delivered by a multidisciplinary team including medical doctors, psychologists, and physical therapists, all trained in self-management support strategies by Bridges Self-Management [50]. In any case of adverse effects of the intervention or in case of detected medical or psychological health problems in need of treatment, suitable actions will be discussed and ensured by the research team. A procedure for handling severe psychiatric conditions is included in the project, where the therapist will immediately consult with senior researchers who are specialist medical doctors and/or psychologists for further management.

#### Relevant concomitant care permitted or prohibited during the trial

Patients will not be withdrawn from any concurrent treatment during the trial.

#### Control group: treatment as usual

The control group will receive the usual health care and rehabilitation services provided in the municipality or other rehabilitation settings. Such services will potentially vary greatly depending on the patient needs and advice they receive at hospitals and services available in their municipalities, ranging from no services to regular contact with specialized or local rehabilitation teams. The services provided will be logged at baseline for all participants allowing comparison with the intervention group at all time-points in terms of content, extent, professionals involved, etc.

### Sample size

The sample size was estimated based on the primary outcome, the Trauma Coping Self-Efficacy Scale questionnaire [26]. The questionnaire is a 9-item scale answered on a scale ranging from 0 (not capable) to 7 (totally capable). A mean difference in the Trauma Coping Self-Efficacy Scale of 0.6 between baseline and follow-up between the groups is considered as a clinical relevant difference (ref). In order to detect a mean between-group difference of 0.6 with an estimated standard deviation of 1, equal allocation to both groups, 80% power, and a significance level of 5%, we will need to include a minimum of 45 patients in each group and a total of 90 participants [51]. With an assumed attrition rate of 20%, 110 patients will be included (i.e., 55 patients in each group). The sample size calculation was done based on the classical randomization arm (RA), and we aim to achieve the same power in the self-selection (SA) arm. However, the SA is considered an exploratory part of this study to evaluate the influence of patients’ treatment preferences. According to a previous longitudinal study at OUH, approximately 310 patients with trauma-related disability from 18 to 72 years of age may meet the inclusion criteria [52]. Based on previous studies, approximately 70–80% will be eligible for inclusion, resulting in 218–249 eligible patients per year.

